| Secondary
a) Efficacy of Atorvastatin in avoiding electric, morphological and biomarkers deterioration;

b) safety of Atorvastatin treatment   | a) Deterioration from baseline of
i) arrhythmia burden (PVC, non-sustained and sustained VA, VF, appropriate ICD shocks); ii) other morphological parameters (ventricular volumes, function, both at ECHO and CMR); iii) ECG parameters; iv) blood parameters;

b) monitoring of AE and patient's well-being. | a)
i) Deterioration from baseline of the frequency of premature ventricular contractions, non-sustained and sustained ventricular arrhythmias, episodes of ventricular fibrillation, appropriate defibrillator shocks (measured by Holter, defibrillator and loop recorder interrogation at T18).
ii) Variation from baseline of morphological parameters, such as ventricular volumes (ml), parietal thicknesses (mm), fibrotic replacement characteristics (mm  ), cardiac functional parameters as ejection fraction (%) or Fractional shortening (%), heart movements (number and extension of bulging and wall motion abnormalities) measured at ECHO and CMR at T18.
iii) Variation from baseline of the electrocardiogram parameters (ms or voltage) at T18.
iv) Variation from baseline of biomarkers at T18 (concentrations, Units).
b)
i) Number and severity of adverse events (blood safety parameters variation and number and severity of patient-reported adverse effects) till T18.
ii) Variation in the score of the psychological questionnaires at T18 respect to baseline. |

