#### **T9 Visit Data collection (9th month +/- 1 month)**

This visit includes:

- IMP supply (3 kits)
- Full physical examination
- Pregnancy test (WOCBP only)
- Blood withdrawal for hepatic and muscle functionality
- 12-lead ECG
- ECHO
- Holter ECG
- ICD/ILR interrogation
- Psychological questionnaires (i.e. SF-36; HADS; IES-R)
- Blood withdrawal for biomarkers
- Patient-reported outcome collection
- Study treatment adherence check
- AE review
- SAE review

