### 9.3. Statistical Analyses

All patient data collected on the CRF will be listed by patient and centre.

The Statistical Analysis Plan, describing details of all the statistical methods and analysis to be applied to trial results is described below. Any change in the planned analysis will be documented. The data will be presented in the clinical study report.

Continuous variables will be reported as mean  $\pm$  standard deviation (SD) if normally distributed, otherwise as median and interquartile range (IQR). For variables with right-skewed distribution, a log-transformation will be considered before analysis, otherwise nonparametric methods will be considered. Categorical variables will be presented as frequencies and percentages. All analyses will be performed using SAS version 9.4 (SAS Institute, Cary, NC, USA).

Possible differences in baseline characteristics of ACM patients belonging to the “Atorvastatin group” and the “placebo group” will be reported in a descriptive manner.

Changes in the variables of interest, measured at different timepoints, will be assessed by paired samples Student's T test or Wilcoxon signed-rank test, and will be compared between groups by Student's T test for independent samples or Mann Whitney's U test.

Differences of treatment effects on the primary and secondary endpoints in the groups will be analysed by using univariate and multivariate regression models, also taking into account possible confounding variables.

Data on the primary endpoint measures will also be available for most subjects before baseline (extended baseline). The analyses will apply time series models to compare the two groups (focusing on rate of change).

Subgroup analyses will account for other medications, underlying genetic mutations or disease stage.

As proof of mechanism, Person's or Spearman's correlation coefficients will be performed to assess possible relationships between endpoints and plasma oxLDL reduction.

Data from the psychological questionnaires will be analyzed by repeated-measures ANOVA models, in order to analyse the variables at different timepoints. For within-patient comparisons, paired sample t-tests will be implemented. Adjustments for possible confounding variables will be considered.

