#### **9.1.4 Missing data**

All reasonable efforts will be made to reduce the rate of missing data, since any method used for imputation for missing observations would be based on untestable assumptions.

In case of impossibility of performing CMR in some patients, the patients will be excluded from the analysis of the specific elements, based on CMR, of the secondary endpoint. The same parameters acquired by ECHO will be used.

Investigators will be trained about the importance of patient retention and full data capture. Also, any reasonable attempts should be made by the Investigators to emphasize continued patient's participation for the full duration of the trial. However, in order to minimize missing data, if a patient cannot refer to the site for a planned follow-up visit, the Investigator will try to obtain any relevant

information from the patients, including documents/laboratory results available from local medical care.

However, if a patient is lost at follow-up after the T9 data collection visit, imputation of missing data may be implemented, when possible, followed by sensitivity analyses.

If the patient drops-out before T9 the patient will be simply excluded from the analysis.

We expect that a larger number of patients will abandon the study if they are in the Atorvastatin group, respect to the Placebo one, since they have probability to experience atorvastatin-related adverse effects. The 15% drop-out rate described in the sample size calculations, takes into account this possibility.

An effort will be made to understand the reasons of drop-outs, mainly to assess whether they are related to the outcomes (ACM-linked events). In this case, to avoid a possible bias (the most serious patients abandon the study) a post-hoc statistical correction may be implemented.

We will try to reduce unused data (collected data items that will not directly link to a result and will therefore not be counted in the final manuscript), and spurious data or spurious inferences, to improve study performance, lower time and costs of collection and storage, and address ethical concerns.

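### The questionnaire analysis (repeated-measures ANOVA) should be replaced by a baseline-adjusted mixed model: a free, minor gain, mainly in precision

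*Protocol*

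**What the plan says.** Section 9.3 of the protocol presents itself as the description of the Statistical Analysis Plan, so the method below is a choice made there and can be assessed.

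- **Model.** "Data from the psychological questionnaires will be analyzed by repeated-measures ANOVA models", with the stated aim of examining the scores across the timepoints.
- **Within-patient tests.** "For within-patient comparisons, paired sample t-tests will be implemented".
- **Covariates.** "Adjustments for possible confounding variables will be considered". The baseline score is not named.
- **General rule in the same section.** "Differences of treatment effects on the primary and secondary endpoints in the groups will be analysed by using univariate and multivariate regression models". Nothing says whether this regression or the ANOVA decides the questionnaire result.
- **Endpoint.** Section 4 lists the questionnaires under secondary objective b (safety and well-being), measured as "Variation in the score of the psychological questionnaires at T18 respect to baseline". Section 8.1.4 schedules them at T0, T9 and T18.
- **Drop-out.** Section 9.1.4 states: "We expect that a larger number of patients will abandon the study if they are in the Atorvastatin group". It gives no rate by arm. Patients lost before T9 are excluded from the analysis. For losses after T9, imputation is optional, followed by sensitivity analyses.
- **Imputation elsewhere.** Section 8.2.3 commits without qualification to multiple imputation of missing data, with a sensitivity analysis.

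**The concern.** The endpoint is one contrast: the arm difference in change from T0 to T18. With T0 as one of the ANOVA's timepoints, that contrast compares mean change scores. A randomised comparison is estimated more precisely when the baseline score is a covariate, and here that costs nothing because the score is already collected.

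The second issue is conditional. A classical repeated-measures ANOVA keeps only patients with all three scores. If it is run that way without imputation, a patient who completes T9 and leaves before T18 contributes nothing, although the T9 score is in hand. If those who leave had been worsening by T9, and more of them are on atorvastatin, the remaining completers look somewhat too well in that arm. For a well-being outcome listed under safety, that is the less comfortable direction.

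**Working it through.** **The plan's own figures.** The protocol gives no power or precision for the questionnaires. Its 44 per group comes from the strain endpoint (Section 9.1: difference 2.4, SD 4.5, one-sided 5%, 80% power): n = 2 × (1.645 + 0.842)² × (4.5/2.4)² = 43.5, so 44 per group, as stated. With 102 randomised and 15% drop-out, 102 × 0.85 ≈ 87 patients reach T18, so a strict complete-case analysis loses about 15. These figures serve only to set the number of completers.

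**Assumptions not in the documents.** Equal score SD at T0 and T18; T0-T18 correlation r from 0.3 to 0.8; drop-out of 20% on atorvastatin and 10% on placebo.

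**Precision.** In SD² units, a change score has variance 2(1 − r) and a baseline-adjusted score has 1 − r². The ratio is 2/(1 + r). The smallest detectable difference at 44 per arm (two-sided 5%, 80% power) is (1.960 + 0.842) × √(2/44) × √variance.

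| r | Variance ratio, change to adjusted | Detectable, change (SD) | Detectable, adjusted (SD) |
|---|---|---|---|
| 0.3 | 1.54 | 0.71 | 0.57 |
| 0.5 | 1.33 | 0.60 | 0.52 |
| 0.7 | 1.18 | 0.46 | 0.43 |
| 0.8 | 1.11 | 0.38 | 0.36 |

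At r = 0.6, with a score SD of 10 and 44 completers per arm, the SE is √(2 × 80/44) = 1.91 for change and √(2 × 64/44) = 1.71 for baseline-adjusted completers. The variance ratio is 80/64 = 1.25. This gain needs only the covariate, not the T9 score.

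**Bias.** In the simulation there were 51 per arm, three visits with equal correlation r, no true effect, higher scores meaning worse, and 4,000 trials per setting. Drop-out was 20%/10%, either half before T9 at random and half after, or all after T9. Drop-out after T9 was either random or dependent on worsening between T0 and T9. Entries are the mean estimate in SD; a negative value favours atorvastatin.

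| Drop-out after T9 | r | Complete-case change | Complete-case, baseline-adjusted | Mixed model using T9 |
|---|---|---|---|---|
| Random | 0.5 | 0.002 | 0.001 | 0.000 |
| Worsening, both arms, half late | 0.5 | −0.038 | −0.021 | −0.005 |
| Worsening, both arms, all late | 0.5 | −0.051 | −0.026 | 0.003 |
| Worsening, atorvastatin only, half late | 0.5 | −0.071 | −0.035 | −0.001 |
| Worsening, atorvastatin only, all late | 0.5 | −0.129 | −0.066 | −0.003 |
| Worsening, both arms, half late | 0.7 | −0.023 | −0.015 | 0.002 |
| Worsening, atorvastatin only, all late | 0.7 | −0.094 | −0.066 | 0.002 |

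A separate simulation used visit correlations of 0.60 to 0.70 and 13% to 15% drop-out after T9, dependent on the T9 score. Its bias was at most 0.1 point on a scale with SD 10, or 0.01 SD.

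At r = 0.5 the empirical SEs were about 0.21 for complete-case change, and 0.18 to 0.19 for both baseline-adjusted analyses. Using the T9 score therefore adds almost no precision. What it adds is protection against bias.

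**The case against.** The strongest case against is that repeated-measures ANOVA is a valid method in a 1:1 randomised trial, that this is an unpowered secondary outcome, and that preferring a mixed model is refinement. That stands as a limit on severity. Several stronger readings are also tempting, and the documents do not support them.

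- *The plan deletes every incomplete patient.* Not for losses after T9. Section 9.1.4 allows imputation and Section 8.2.3 promises it. The wording also leaves the estimation method open, and such models can be fitted by likelihood using all visits. Deletion is explicit only before T9, and the model proposed here does not recover those patients either, since they have no post-baseline score.
- *The baseline is wasted.* T0 is one of the repeated measures and enters the contrast. The loss is one of efficiency. Optional adjustment and regression models are also mentioned, though neither is fixed for these scores.
- *Within-patient t-tests stand in for the treatment comparison.* The protocol labels them as within-patient and provides between-group comparisons separately.
- *Harm would be hidden.* The bias is small in every scenario tried and reaches 0.13 SD only when informative drop-out is confined to atorvastatin and falls entirely after T9. Section 8.5 rests safety mainly on blood tests and patient-reported adverse events, and adverse events are reviewed at every post-baseline contact.

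The efficiency argument survives all of this. So does the need to name one deciding model and one imputation rule.

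**Conclusion.** The point holds as a free improvement of minor severity. The planned T0-to-T18 contrast has 18% to 33% more variance than a baseline-adjusted one at an assumed correlation of 0.7 to 0.5. Put the other way, adjustment brings the variance down to (1 + r)/2, or 85% to 75%, of its present value. If the ANOVA is run on complete cases without imputation, a bias of about 0.01 to 0.13 SD towards atorvastatin is possible. Its size depends on assumed drop-out rates and mechanisms, and it vanishes if drop-out is random. The mixed model stayed within 0.005 SD of zero in the 20%/10% settings, where drop-out depended on observed scores; drop-out driven by unobserved scores was not examined. The gain is mainly precision from baseline adjustment, with modest protection against bias. The strain endpoint and the sample size are untouched.

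**What to change.** In Section 9.3, replace the questionnaire sentences with wording to this effect: for each questionnaire score, T9 and T18 values will be analysed by a likelihood-based mixed model for repeated measures with baseline score, arm, visit and arm-by-visit interaction, using all observed data; the estimate is the arm difference at T18 with its confidence interval; within-arm changes and paired tests are descriptive only. State that this model, and not the general regression rule, decides the questionnaire result.

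Reconcile Section 9.1.4 (imputation optional) with Section 8.2.3 (imputation definite) for these outcomes, for example by placing multiple imputation among the sensitivity analyses of the mixed model.

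The cost is a wording change. The model can be fitted in the SAS version named, on data already scheduled, with no extra patients or visits.

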**Overall Design:**

This is a multicenter, prospective, randomized, clinical study: Atorvastatin 80mg/day or placebo will be administered for 18 months to 102 ACM patients, and the endpoints will be tested.

Atorvastatin has the potential to target ACM progression, thus reducing disease burden and related healthcare costs. The repurposing strategy drastically cuts the timing for its effective and economical use in ACM, respect to new drug development.

The clinical/biological data collected in the trial will also be used to validate a disease progression prediction model, and a to identify markers associated to Atorva differential response, with the use of innovative AI based tools.

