| Tertiary/Exploratory
a) Validation of prediction models of ACM progression;

b) prediction of differential response to Atorvastatin treatment. | a) Testing the prediction models on the prospectively collected clinical, biological, genetic, and radiomics data of the placebo cohort;

b) testing the association of prospectively collected clinical, biological, genetic, and radiomics data of the Atorvastatin cohort with outcome.                       | a) Verification in terms of sensitivity, specificity, overall predictive performance of the correspondence between the predicted outcome (by different prediction models) and the actual variation at T18 of the clinical, biological, genetic, and radiomics variables of the placebo cohort;

b) association coefficients of the baseline clinical, biological, genetic, and radiomics variable of the Atorvastatin cohort with endpoints outcomes.                                                                                                                                                                                                                                                                                                                                                                                                                                                                                                                                                                                                                                                                     |

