For the third objective, different AI models will be created to exploratively assess the association between a large number of potential predictors (below referred as variables) and the response to treatment, in terms of primary and secondary study endpoints. In this case, the test cohort will be

the “Atorvastatin Group”. Standard clinical variables and symptoms, together with biomarkers (as plasma lipids, inflammatory, cardiac damage and fibrosis markers), genotype and image-derived features (extracted from ECHO and CMR), collected at T0, will be taken into account as possible predictive variables to define the models. In particular, image-derived features will be obtained by radiomics analysis, which extracts a large number of quantitative characteristics that fail to be detected by the naked eye. Different models will be developed to describe the association of the previously described variables, either as single domains or combined, with the endpoint outcomes at T18 of the patients receiving Atorvastatin. Several feature selections (e.g. filter and wrapper methods) and AI algorithms (e.g. random forest, support vector classifier, k-nearest neighbors) will be used to develop multi-modal models for the prediction of response to Atorvastatin. In view of the relatively small sample size involved, a nested cross-validation approach will be used to overcome test set selection bias. The final model will be obtained by re-training the best performing pipeline in nested cross-validation on the entire dataset, with hyperparameter values tuned with a regular k-fold cross-validation on the whole dataset. Performance metrics will include balanced accuracy, sensitivity, specificity and f1 score.

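### Exploratory objective b seeks predictors of differential response to atorvastatin but analyses the atorvastatin arm alone, which cannot separate effect modifiers from prognostic markers or regression to the mean

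*Protocol*

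**What the plan says.** The objectives table (Synopsis and Section 4) gives exploratory objective b as "prediction of differential response to Atorvastatin treatment". The Synopsis, under Overall Design, states the same aim: "to identify markers associated to Atorva differential response, with the use of innovative AI based tools".

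The analysis attached to that aim uses one arm throughout:

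- Endpoint (Section 4): "testing the association of prospectively collected clinical, biological, genetic, and radiomics data of the Atorvastatin cohort with outcome".
- Outcome measure (Section 4): "association coefficients of the baseline clinical, biological, genetic, and radiomics variable of the Atorvastatin cohort with endpoints outcomes".
- Method (Section 9.3): the Atorvastatin group is named as the test cohort, and T0 variables are associated "with the endpoint outcomes at T18 of the patients receiving Atorvastatin". The resulting models "will be used to develop multi-modal models for the prediction of response to Atorvastatin".

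The placebo cohort appears in the third objective only under objective a, where progression models are tested. Section 9.3 labels the work exploratory: "For the third objective, different AI models will be created to exploratively assess the association between a large number of potential predictors". On model choice it says: "The final model will be obtained by re-training the best performing pipeline in nested cross-validation on the entire dataset".

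**The concern.** Differential response means that the benefit of atorvastatin over placebo changes with a baseline feature. Judging that requires knowing how the same feature relates to outcome without the drug. The plan leaves that comparison out of objective b, although randomisation supplies it.

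The protocol's own reasoning sharpens the problem. Section 5.5 justifies placebo partly by the need to control for spontaneous fluctuation of the disease. Objective a presupposes that clinical, biological, genetic and radiomic data can predict progression in placebo patients. If they can, the same features can be expected to predict outcome in treated patients too, and objective b would report them as predictors of response. Image-derived ECHO features are also among the candidate predictors. If they include baseline strain or a close correlate, such a feature is mathematically linked to change in strain even when the drug does nothing.

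At stake is the interpretation of one exploratory result: a model presented as predicting response to atorvastatin that may only predict slow progression.

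**Working it through.** **Inputs from the protocol.** Section 9.1: 44 evaluable patients per group, difference 2.4 strain points, SD 4.5, one-sided alpha 0.05, power 80%. Section 5.5: untreated loss of 2.4 points over 18 months, SD 4.5.

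**Assumptions not in the protocol.** The SD of 4.5 is read as the SD of the 18-month change. Marker-change correlations are 0.3, 0.4 and 0.5. Baseline strain SD is 5, 6 or 7, with equal variance at T18. Tests are univariate and two-sided at 5%. Each setting has 4,000 simulated trials.

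**1. The plan's own figure.** n per group = 2(1.645 + 0.842)² × (4.5/2.4)² = 43.5, rounded up to 44. The stated size reproduces, so 44 treated patients is the right basis.

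**2. What each analysis estimates.** Write change = a + b·T + c·M + d·T·M + error, with T = 1 for atorvastatin and M the marker. Differential response is d. In the treated arm the slope on M is c + d; in the placebo arm it is c. Treated patients alone give only the sum, so c > 0 with d = 0 looks the same as c = 0 with d > 0. This needs no numerical assumption.

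**3. Illustration.** The prognostic marker has the same slope in both arms (d = 0). The predictive marker acts in the treated arm only (c = 0). Both have the same within-arm correlation r in treated patients. Entries are the percentage of trials with p < 0.05.

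| r | Treated-only, prognostic | Treated-only, predictive | Interaction, prognostic | Interaction, predictive |
|---|---|---|---|---|
| 0.3 | 52.2 | 52.1 | 5.7 | 28.8 |
| 0.4 | 78.8 | 78.1 | 4.9 | 45.9 |
| 0.5 | 94.4 | 94.3 | 5.5 | 68.4 |

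The two treated-only columns agree within simulation error.

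**4. Regression to the mean, no drug effect.** With equal variances, the T0-T18 correlation is ρ = 1 − 4.5²/(2s²) for baseline SD s, and corr(baseline, change) = −√((1 − ρ)/2).

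| Baseline SD s | ρ | corr(baseline, change) | Treated-only significant, % | Interaction significant, % |
|---|---|---|---|---|
| 5 | 0.595 | −0.450 | 87.6 | 5.6 |
| 6 | 0.719 | −0.375 | 73.0 | 5.3 |
| 7 | 0.793 | −0.321 | 57.4 | 5.6 |

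**5. Responder labels.** The planned metrics (balanced accuracy, sensitivity, specificity, F1) need a class label. Suppose that label were no worsening, and suppose a full effect (mean change 0 on atorvastatin, −2.4 on placebo, SD 4.5). Then 50% of treated patients would be responders, as would 1 − Φ(2.4/4.5) = 29.7% of placebo patients. The ratio is 0.297/0.50 = 0.59, so the label itself would not isolate a drug response.

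**The case against.** **Status.** The objective is exploratory and its stated measure is association coefficients. No decision in the trial depends on it. This stands and limits the weight of the point, but it does not make a one-arm association answer a question about differential response.

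**Other provisions in the protocol.** Section 9.3 also plans between-group regression models, subgroup analyses by medication, mutation and disease stage, and an extended baseline to study rate of change. Objective a yields prognostic information from placebo patients. These are relevant, but none is tied to the response models, no interaction test is named, and no contrast between the two cohorts' models is planned. Nested cross-validation guards against overfitting, not against a missing comparator.

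**Left to a separate analysis plan.** Detail could be, but the cohort is not left open: the objectives table and Section 9.3 both fix it.

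**The simulation is not the planned analysis.** This is correct. Univariate tests at assumed correlations stand in for cross-validated classifiers, so a reader who took 50 to 95% as this trial's error rate would go too far. The non-identifiability in step 2 does not depend on those figures.

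**Stronger readings to avoid.** A reader might infer that the treated-only models find nothing but prognostic markers and regression to the mean. They do not: true effect modifiers are detected at the same rate, and the defect is that the kinds cannot be told apart. A reader might also infer that the reported model performance is bound to be optimistic. The protocol says that the best pipeline will be retrained, not that its winning score will be the reported performance. The number of pipelines and their dependence are not given, so no size can be attached.

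**Conclusion.** The point holds in a limited form. The stated objective (differential response) and the stated analysis (atorvastatin arm only) do not match, and followed exactly the plan cannot distinguish effect modifiers from prognostic markers or regression to the mean. That conclusion follows from the design.

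The sizes are illustrative. A prognostic marker is flagged in about 50 to 95% of treated-only tests, the same as a predictive one, against about 5% for a two-arm interaction test (44 per arm, r = 0.3 to 0.5). Baseline strain alone is flagged in about 57 to 88% when the drug does nothing (baseline SD 5 to 7).

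The consequence is confined to exploratory objective b; primary and secondary conclusions are untouched. It should be corrected because the data that answer the question are already being collected.

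**What to change.** - **Analysis.** In Section 9.3 and the objectives table, fit the objective b models on both randomised arms. Target the treatment-by-predictor interaction, or fit each arm separately and take the difference in predictions. Include baseline strain as a covariate.
- **Wording.** If an atorvastatin-only model is kept, describe it as prognostic under treatment, not as a predictor of response.
- **Minor.** If the best of several pipelines is chosen on its nested cross-validation score, report the outer-loop performance of the whole selection procedure, not the winner's score.

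**Cost.** There are no new patients, visits or measurements, since both arms follow the same Schedule of Activities. Some re-coding is needed. The real price is precision: with 88 patients, interaction power for a single marker is about 29%, 46% and 68% at r = 0.3, 0.4 and 0.5 under the assumptions above. Screening many features with any control for multiplicity would lower it further. Findings should be presented as hypothesis-generating.

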## 9. Statistical Considerations

### 9.1. Sample Size Determination

A power analysis estimated that 88 patients (44 per group) will be sufficient to observe at T18 a significant ( $\alpha=0.05$ ) mean absolute difference between the two groups of 2.4 points of RV free wall longitudinal strain (%), hypothesizing a standard deviation of 4.5% and with a power of 80%. The statistical test used to calculate the sample size was an independent one-sided T test. Assuming a drop-out rate of 15% during the study, the total sample size is 102 patients (51 per group). Assuming a screening failure of about 5%, 110 patients will be screened.

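### Section 9.3 chooses the response-model pipeline on the same nested cross-validation scores that are meant to remove selection bias, so the winner's score is optimistic

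*Protocol*

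**What the plan says.** Section 9.3 describes models that link baseline variables, "either as single domains or combined, with the endpoint outcomes at T18 of the patients receiving Atorvastatin". The named variable groups are clinical variables and symptoms, biomarkers, genotype and image-derived features. Feature selection is by several methods, with filter and wrapper methods as examples. The algorithms are also several, with random forest, support vector classifier and k-nearest neighbours as examples.

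Because the sample is small, "a nested cross-validation approach will be used to overcome test set selection bias". The next step reads: "The final model will be obtained by re-training the best performing pipeline in nested cross-validation on the entire dataset". Hyperparameters for that final fit are tuned by ordinary k-fold cross-validation on the whole dataset. The listed metrics are balanced accuracy, sensitivity, specificity and F1.

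The section labels this work exploratory. It sets no number of pipelines, definition of response, fold scheme or threshold for calling a model predictive. It describes no held-out set or permutation reference for the response model. The placebo cohort serves exploratory objective a, the progression models, not this one. Section 9.3 presents its own text as the description of the statistical analysis plan.

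**The concern.** Nested cross-validation separates two jobs. The inner loop chooses, and the outer loop scores what was chosen on patients who played no part in the choice. This protects the score only if every choice is made inside. Here the last choice, which pipeline wins, is made on the outer-loop scores. The outer loop then becomes a selection set, and the highest of several noisy scores tends to lie above the true performance of the pipeline that produced it. The selection rule therefore brings back, one level up, the bias that nesting was introduced to remove.

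Refitting the winner on all patients is acceptable in itself, but it leaves no unused data. If an accuracy is quoted for the final model, the text offers only the winner's nested score. At stake is an overstated accuracy for a model of response to Atorvastatin, in an arm of about 44 evaluable patients where scores are noisy and the upward shift can be large.

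**Working it through.** **Size of the dataset.** Section 9.1 states: "A power analysis estimated that 88 patients (44 per group) will be sufficient to observe at T18". The inputs are a "mean absolute difference between the two groups of 2.4 points of RV free wall longitudinal strain", an assumed SD of 4.5 points, a target power of 80%, alpha 0.05, and "The statistical test used to calculate the sample size was an independent one-sided T test". By the normal formula, n per arm = 2 × (1.645 + 0.842)² × 4.5² / 2.4² = 43.5, rounded up to 44. The protocol's figure is reproduced, and the response model has about 44 Atorvastatin patients.

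**Number of pipelines.** The document fixes none, so three cases are shown, counted from the named examples:
- 3: one predictor set, one feature selection, three algorithms.
- 6: the combined predictor set, two feature selections × three algorithms.
- 30: the four named groups plus all combined (5 sets) × 2 × 3.

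**Nominal cut.** With 44 patients and an even split, P(X ≥ 28 | 44, 0.5) = 0.048. This corresponds to a balanced accuracy of 28/44 = 0.636.

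**Null simulation.** There were 199 data sets of 44 patients, 22 responders and 22 non-responders, with every feature pure noise (20 clinical, 25 biomarker, 10 genotype, 200 imaging). Five outer and four inner folds were used, with a filter or recursive elimination, and bagged trees (standing in for random forest), support vector classifier or k-nearest neighbours. The responder split, feature counts and folds are assumptions.

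| Procedure | Mean balanced accuracy | ≥ 0.60 | ≥ 28/44 | ≥ 0.70 |
|---|---|---|---|---|
| One pipeline fixed beforehand | 0.499 | 11% | 11% | 3% |
| Best of 3 | 0.541 | 20% | 17% | 4% |
| Best of 6 | 0.575 | 33% | 23% | 6% |
| Best of 30 | 0.653 | 82% | 67% | 26% |
| Pipeline chosen in the inner loop (from 30) | 0.497 | 10% | 6.5% | 2% |

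Optimism is the winner's mean minus the fixed pipeline's mean: 0.541 − 0.499 = 0.042, 0.575 − 0.499 = 0.076, and 0.653 − 0.499 = 0.154. The 95% half-widths for the 28/44 column are about 5, 6 and 6.5 percentage points for 3, 6 and 30 pipelines.

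A fixed pipeline passes the nominal 4.8% cut somewhat too often (11% for this one, 8% averaged over all 30), because cross-validated predictions are not independent. So the selection effect should be judged against 8% to 11% rather than against 4.8%. The means are free of this complication: the fixed pipeline sits at chance.

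**Cross-check by formula.** If pipelines were independent, P(best ≥ 28/44) = 1 − (1 − 0.048)^M, which gives 14% for M = 3, 26% for M = 6 and 77% for M = 30. With a common correlation of 0.5 between scores (normal approximation) the figures are about 11%, 18% and 39%. In the simulation the mean correlation was 0.16 across all 30 pipelines and 0.55 within the six combined-set pipelines.

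**Second simulation.** Another run with 98 null data sets, 30 pipelines, five outer and three inner folds gave a winner's mean of 0.648, with 61% reaching 28/44. With the choice moved to the inner loop these became 0.502 and 6%.

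**The case against.** Several points on the other side have force.

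- **The size is not a property of the protocol.** The options are given as examples and no count is fixed. The sentence on feature selections and algorithms speaks of multi-modal models, so the contest may be among combined models only. That means 6 pipelines from the named options, with 23% reaching 28/44. This stands, and it is why a range is given. A reader might infer that the plan would yield an apparently predictive model in most trials with no signal. That holds only with about 30 pipelines in one contest and a cut near 0.60 to 0.65. With 3 or 6 pipelines, or a cut of 0.70, it does not.
- **No success rule exists.** A reader might infer that the objective would be declared met on noise, or that the rule cannot tell a real predictor from none. The documents do not support either reading. Section 4 gives association coefficients as the measure for this objective, section 9.3 sets no threshold, and a rule for choosing a model is not a rule for claiming success. Two-class balanced accuracy also has a known chance level of 0.5.
- **The harmful step is not explicit.** Section 9.3 does not say outright that the winner's nested score will be reported as the final model's accuracy. Choosing a pipeline to refit does no harm; quoting its score does. This stands as a limit. But performance metrics are promised, and the text offers no other out-of-sample estimate.
- **The analysis is exploratory.** This limits the consequence. It does not make a score known to be biased upward acceptable when an unbiased one is available from the same data.

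**Conclusion.** The concern holds as to mechanism and direction. Section 9.3 states a selection rule that defeats the stated purpose of its own nested cross-validation, and nothing else in the protocol corrects this for the response model. If the winner's nested score is quoted as accuracy, it is optimistic under a pure-noise null by about 0.04 balanced accuracy with 3 pipelines, 0.08 with 6 and 0.15 with 30. The chance of reaching 28 of 44 correct is about 17%, 23% and 67% respectively.

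These sizes rest on 44 patients, an even responder split, and assumed feature counts and fold scheme. More pipelines would raise them; fewer, or more highly correlated ones, would lower them. The impact is confined to the exploratory objective: the primary and secondary analyses, the sample size and safety are untouched. The change is worth making because it is nearly free.

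**What to change.** In the third-objective text of section 9.3, make the whole choice of pipeline (predictor domains, feature selection, algorithm and hyperparameters) part of the inner loop. Report the outer-loop score of that complete procedure as the performance estimate. The final model may still be obtained by running the same procedure on all Atorvastatin patients, but the winning pipeline's own nested score should not be quoted as its accuracy.

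Rerunning the whole procedure on permuted outcome labels would give a useful reference distribution. This is an optional addition, not a required rule for making a claim.

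The cost is one paragraph of protocol text and extra computing time, with no new patients or data. The reported accuracy will be lower. The change is best written before the blind is broken, while it still counts as pre-specified.
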